### 5.23. Statistical Analysis Methods

- Basic statistical methods

All statistical analyses will be conducted using SPSS 26.0 and GraphPad Prism 9.0 software, statistical analysis will be primarily descriptive. Quantitative data will be presented as median (interquartile range), and qualitative data will be presented as n (%). The differences between groups of quantitative data will be performed using student's t tests or Wilcoxon non-parametric tests. Qualitative variables will be tested with chi-square tests or Fisher's exact tests. The methods of Kaplan-Meier will be used to estimate the time-to-event data. All tests will be calculated with a two-sided significance level of 0.05.

- Safety analysis

Summary tables for adverse events have to include all AEs that occurred in the whole period of study. The correlation between treatment and AEs will be determined by the principal investigator.

- Effectiveness analysis

Proportions with 95% confidence intervals will be calculated for the efficacy endpoint.

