# Inclusion, Exclusion Criteria and Assignment Methods

## 6.1 Inclusion Criteria

1. 18-60 years of age;
2. Confirmed diagnosis of ITP for at least 6 months with an insufficient response to first-line treatment drugs (IVIG, glucocorticoids), and thrombopoietic agents (recombinant human thrombopoietin (rhTPO), eltrombopag, avatrombopag, romiplostim, etc.) and anti-CD20 monoclonal antibody (rituximab) in second-line, or failed to splenectomy or subsequent relapse;
3. Subjects who received splenectomy or rituximab must have finished the therapy more than 3 months prior to UC-MSCs inclusion;
4. Platelet counts < 30×10^9^/L with bleeding;
5. Expected survival time for at least 6 months;
6. The function of liver and kidney is less than 1.5 times the upper limit of normal value, and the physical examination is qualified;
7. Subjects are allowed to maintain stable ITP concomitant treatment. The dose of glucocorticoids (less than or equal to 0.5mg/kg prednisone or equivalent dose of glucocorticoids) and thrombopoietin receptor agonists should be stable for at least 4 weeks, and the dose of azathioprine, danazol, cyclosporine A, mycophenolate mofetil, tacrolimus, and retinoic acid should be stable for at least 12 weeks;
8. Be able to understand the purpose and risks of the study and provide informed consent in accordance with national and local privacy regulations;
9. Cardiac function: Grade 2 or below according to the New York Society for Cardiac function;
10. ECOG physical status score ≤ 2.

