## 6.2 Exclusion Criteria

1. Subjects with primary disease of important organs (liver, kidney, heart, etc.), or with immune system diseases;
2. Secondary thrombocytopenia caused by various reasons, such as connective tissue disorders, bone marrow hematopoietic failure disease, myelodysplastic syndrome, malignancy, drugs, inherited thrombocytopenia, common variable immune deficiency, lymphoma, etc.
3. Subjects infected with human immunodeficiency virus (HIV);
4. Uncontrollable and active infections during the screening period, including hepatitis B, hepatitis C, cytomegalovirus, EB virus, or positive syphilis antigen;
5. Subjects with extensive and severe bleeding, such as hemoptysis, upper gastrointestinal hemorrhage, intracranial hemorrhage;
6. Subjects with heart disease that requires treatment or hypertension that has been judged by researchers to be poorly controlled currently;
7. Subjects with any venous or arterial thrombosis, atherosclerosis, and other diseases;
8. Subjects with a history of malignant solid tumor or have received allogeneic stem cell transplantation or organ transplantation;
9. Subjects with mental disorders who are unable to sign normal informed consent and conduct trials and follow-up;
10. Subjects whose toxic symptoms caused by pre-trial treatment have not disappeared;
11. Subjects with other serious diseases that may limit their participation in this trial (diabetes; severe cardiac insufficiency; myocardial obstruction or unstable arrhythmia or unstable angina pectoris in the last 6 months; gastric ulcer; active autoimmune disease, etc.);
12. Subjects with septicemia or other irregular bleeding;

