## 14.2 Evaluation Criteria of Efficacy

- Main efficacy criteria:

umbilical cord-derived MSCs infusion can increase the platelet count of the subjects, indicating that the drug is effective.

Evaluation criteria of efficacy:

According to the international consensus of ITP:

- complete response (CR): platelet count ≥ 100 × 10^9^ /L and no bleeding after treatment.
- response (R): platelet count ≥ 30 × 10^9^ /L and at least doubling of the baseline count, and no bleeding after treatment.
- No response (NR): platelet count <30 × 10^9^ / L or less than doubling of the baseline count or bleeding after treatment.
- Relapse: platelet count below 30 × 10^9^/L, or less than doubling of the baseline count, or bleeding, after the achievement of CR or R.

When defining a CR or R, it should be tested at least twice with an interval of at least 7 days.

- Safety efficacy criteria:

The subjects have no obvious adverse reactions caused by umbilical cord-derived MSC infusion, normal vital signs, no hepatitis B, hepatitis C, and other virus infections, and no abnormal organ function. There was no significant difference (P > 0.05) in heart, liver, and renal function between objects before and after treatment, indicating that umbilical cord-derived MSCs have no obvious side effects and are safe.

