# Quality Control and Quality Assurance

## 18.1 Quality Control

1. Determination of study protocol: The clinical study protocol is discussed and negotiated by all investigators participating in this clinical study, and is submitted to the Ethics Committee for approval after reaching a consensus on revision.
2. Control measures of laboratory quality: The manufacturers of umbilical cord MSCs have standardized testing indicators, standard operating procedures, and quality control procedures.
3. Qualification of investigators: Investigators participating in clinical research must have the professional expertise, qualifications and abilities of clinical research, pass the qualification examination. The study needs relatively fixed personnel.
4. Pre-study training: Through pre-study training, investigators can fully understand the clinical study protocol and the specific contents of each index.
5. The criteria for determining abnormalities in laboratory tests are based on the normal reference range of the test unit.
6. All observations and findings in clinical studies should be verified to ensure the data’s reliability and that the conclusions in clinical studies are derived from the original data. Ensure that there are corresponding data management measures in the clinical study and data processing stages.
7. Proactive measures should be taken for possible dropouts to control the shedding rate within 20%.
8. The investigators should ensure that the data are entered into the CRF in a correct (consistent with the actual situation of the subjects), complete (no missing items), clear (neat handwriting and easy to identify), and timely manner according to the original observation records of the subjects.

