## Virological examination: Hepatitis B, HCV, HIV, syphilis antibodies, EB virus antibodies, cytomegalovirus antibodies, herpes simplex virus antibodies, etc.

## B-ultrasound: B-ultrasound of liver, gallbladder, pancreas, spleen, and kidney.

## Pharmacokinetic study: A total of 11 blood samples should be collected from female subjects before and 30 minutes, 1h, 2h, 4h, 8h, 16h, 24h, 48h, 72h, 96h after the first infusion of umbilical cord MSCs; all of them are collected from peripheral blood vessels and no less than 2ml. The blood sample collection tubes are anticoagulated with heparin calcium and are taken to mark the subject's medical record number, the time, and the date of blood collection. The collected specimens should immediately be stored in a special location in the refrigerator at 2-8 ℃ and marked.

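### The safety criterion in Protocol 14.2 asks for normal findings rather than no new or worsened findings, so an eligible subject can miss it before the first infusion

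*Protocol*

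**What the plan says.** Protocol 14.2 sets out, under its safety criteria, when the product counts as safe. There are two sentences.

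- The first opens with a causal condition, "The subjects have no obvious adverse reactions caused by umbilical cord-derived MSC infusion", and then lists further conditions: "normal vital signs, no hepatitis B, hepatitis C, and other virus infections, and no abnormal organ function". The causal qualifier belongs to the adverse reactions only. The other items carry no grade, threshold, time point or baseline.
- The second adds a statistical condition, "There was no significant difference (P > 0.05) in heart, liver, and renal function between objects before and after treatment", and draws the conclusion of safety. Section 5.23 fixes the level: "All tests will be calculated with a two-sided significance level of 0.05".

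Four other places bear on the first sentence.

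- 6.1, item 6 (entry limit): "The function of liver and kidney is less than 1.5 times the upper limit of normal value".
- 18.1, item 5 (what counts as abnormal): "The criteria for determining abnormalities in laboratory tests are based on the normal reference range of the test unit".
- 6.2, item 4 (which infections bar entry): "Uncontrollable and active infections during the screening period". HIV is excluded separately under item 3.
- Footnote on virological examination to the attached flow chart: "Hepatitis B, HCV, HIV, syphilis antibodies, EB virus antibodies, cytomegalovirus antibodies, herpes simplex virus antibodies, etc". The chart places these tests before enrolment and at W4 and W16.

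**The concern.** A criterion for concluding that a product is safe should respond to what happens after the product is given. The first sentence of 14.2 responds to the subject's state, whatever its origin. A subject who enters with a mildly raised liver or kidney value, as the entry criteria allow, and who stays exactly there for 16 weeks has been unaffected by the infusion. By the words of 14.2 that subject still does not show the required normal organ function.

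The primary objective is safety, and 14.2 is where the protocol says when the product may be called safe. If pre-existing or incidental abnormality counts against it, the criterion either gives a misleading answer or has to be reinterpreted once the data are known. The sentence also does not say whether one subject with one abnormal finding is enough to fail it, so two analysts could reach different conclusions from the same data.

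**Working it through.** **1. The conflict in the text, without any probability.**

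| Item in 14.2, first sentence | What entry and testing allow | Consequence |
|---|---|---|
| Organ function not abnormal | 6.1 item 6 admits values between 1 and 1.5 times the upper limit; 18.1 item 5 takes the reference range as the standard | An eligible subject can be outside normal at screening |
| No viral infection | 6.2 item 4 bars uncontrollable, active infection; EBV, CMV and HSV are tested by antibody | Antibody present at screening may be found again at W4 and W16; 14.2 does not say how to classify it |
| Vital signs normal | 18.1 item 5 covers laboratory tests only; 6.2 item 6 bars hypertension only if judged poorly controlled | No definition of normal and no baseline |

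**2. Whether the second sentence cures this.** It compares cardiac, hepatic and renal function before and after treatment, so it does refer to baseline. But it is a group test, it leaves out vital signs and virology, and it does not redefine abnormal organ function in the first sentence.

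The two sentences can also disagree.

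- A subject whose liver value lies between 1 and 1.5 times the upper limit before and after treatment contributes no change to the test, yet misses the first sentence.
- With no true effect, three independent two-sided tests at 0.05 are all non-significant with probability 0.95^3 = 0.857.
- With a true mean shift of 0.5 standard deviations of the within-subject change, a paired t test in 15 subjects is still non-significant with probability 0.562 (1 minus the noncentral-t power of 0.438).

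The first sentence can therefore fail a harmless product, while the second can pass one that shifts organ function.

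**3. Number of subjects.** Section 7 gives 9 to 12 in escalation plus 6 in expansion: 9 + 6 = 15, which matches its stated minimum of 15, and 12 + 6 = 18.

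**4. Size, if the sentence is read as covering all subjects.** Let q be the share of subjects with at least one abnormality unrelated to the product. The documents give no value, so q is assumed over a range. Taking subjects as independent, a harmless product meets the sentence with probability (1 − q)^N.

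| q (assumed) | N = 15 | N = 18 |
|---|---|---|
| 1% | 0.99^15 = 0.860 | 0.835 |
| 5% | 0.95^15 = 0.463 | 0.397 |
| 10% | 0.90^15 = 0.206 | 0.150 |
| 20% | 0.80^15 = 0.035 | 0.018 |

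The probability falls below 5% at N = 15 only when q exceeds 1 − 0.05^(1/15) = 0.181, about 18%.

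**The case against.** Several points on the other side stand.

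- **Other safety rules exist.** Section 3.2 evaluates primary safety by how often adverse events and serious adverse events occur and how severe they are, graded by CTCAE 5.0. Escalation follows the dose-limiting toxicity definition after 5.1, which covers only newly appearing, infusion-related events of grade 3 or higher. No escalation or stopping passage refers to the 14.2 sentence. This limits the damage.
- **The protocol thinks in terms of change elsewhere.** 15.2 item 6 records clinically significant abnormal changes and follows them to normal or to baseline. This shows the probable intent. It also shows that the missing qualifier in 14.2 is a drafting fault.
- **Virology.** 14.2 speaks of infections, not of antibody positivity. The synopsis and 14.1 place viral infection among observations made from the first infusion to week 16, so infection arising after infusion is the natural reading. A reader might infer that old EBV, CMV or HSV antibody counts as failure; the documents do not say that. What remains is that the sentence does not rule it out.

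Two stronger readings are tempting and are not supported. One is that every subject must be normal throughout. The text says only that the subjects are, with no rule for combining them. The other is that a harmless product would almost always fail. That depends on q, which is not given, and at q = 1% the product passes with probability 0.86. Multiplying over 10 chemistry analytes at 4 visits gives far smaller figures. But it requires 40 independent results per subject and the equation of one out-of-range value with abnormal organ function. The protocol supports neither.

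**Conclusion.** The point holds in a limited form. The first sentence of the safety criteria states vital signs and organ function as absolute conditions, and for organ function this conflicts with 6.1 item 6 read together with 18.1 item 5. That conflict needs no assumed rate. The lack of a rule for combining subjects, and the failure to separate viral markers present at screening from new ones, are also on the face of the text.

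The numerical consequence is conditional. It assumes an all-subjects reading, independent subjects and a background share q that the protocol does not state. On that basis the chance that a harmless product meets the sentence runs from 0.86 (q = 1%) to 0.035 (q = 20%) in 15 subjects. It would be wrong to say that the criterion as a whole ignores baseline, because its second sentence compares organ function before and after treatment. It would also be wrong to call it the trial's only safety rule. The correction is worth making because 14.2 is a stated basis for concluding safety and, as worded, counts pre-existing abnormality against the product.

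**What to change.** Reword the first sentence of the safety criteria in 14.2 so that it counts:

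- vital-sign and laboratory abnormalities that are new, or worse by CTCAE 5.0 grade, relative to the subject's own pre-infusion value;
- viral markers negative at screening and positive at W4 or W16.

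Report the number and percentage of subjects with each, in place of an undefined requirement that the subjects be normal. Reconcile the wording with inclusion criterion 6; which limit is appropriate is for the sponsor to settle. Since the two sentences of the criterion can disagree, say also how the reworded sentence and the before/after test are to be read together.

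The cost is a wording change and a simple shift summary. The flow chart already schedules pre-infusion vital signs, chemistry and virology, chemistry at W4, W8, W12 and W16, virology at W4 and W16, and vital signs through W4. No new assessment is needed.

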**5.2 Statistical Methods**

### 5.21. Sample Size Estimation

Three dose groups will be set in the dose-escalation stage, 3 subjects will be enrolled each time and 9-12 patients will be enrolled in total according to the "3+3" dose-escalation protocol.

There will be 6 patients enrolled in the dose-expansion stage to explore the efficacy.

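### A non-significant before-after test of organ function (P > 0.05) is read as showing that the cells are safe, an inference these sample sizes cannot support

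*Protocol*

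**What the plan says.** Under the safety criteria in Protocol section 14.2, the last sentence reads "There was no significant difference (P > 0.05) in heart, liver, and renal function between objects before and after treatment", and the conclusion attached to that result is that the cells "have no obvious side effects and are safe". The sentence before it sets individual-level conditions: no obvious adverse reaction to the infusion, normal vital signs, and "no hepatitis B, hepatitis C, and other virus infections, and no abnormal organ function". The section does not say how the two sentences combine.

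Section 5.23 says "All tests will be calculated with a two-sided significance level of 0.05" and offers "student's t tests or Wilcoxon non-parametric tests" for quantitative data, worded as comparisons between groups. It also calls the analysis mainly descriptive. Section 5.21 gives the sizes: "3 subjects will be enrolled each time and 9-12 patients will be enrolled in total" in escalation, then "There will be 6 patients enrolled in the dose-expansion stage to explore the efficacy".

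No equivalence margin, power, analyte, time point or analysis level (per dose or pooled) accompanies the P > 0.05 rule.

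**The concern.** Safety is the primary objective (section 3.1), and this sentence says in terms what test result would indicate that the product is safe. A P value above 0.05 can mean that nothing changed, or that the sample was too small or too variable to show a change. The rule does not separate these cases, and it becomes easier to satisfy as patients are fewer or measurements noisier.

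A test of average change is also a poor detector of what an early safety trial most needs to see, which is serious harm in one or a few patients. In a t test on the raw scale, a large rise in a few patients inflates the standard deviation as well as the mean, so the test can stay non-significant. A report that followed the sentence literally could cite such a result as evidence of safety.

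**Working it through.** **Inputs from the protocol.** Two-sided 0.05 and a t or Wilcoxon test (section 5.23). Three patients per dose group, 9 to 12 in escalation, 6 in expansion (section 5.21). Adding up: 3 × 3 + 6 = 15, which reproduces the stated minimum of 15 in section 7; at the upper end 12 + 6 = 18. The protocol states no power or margin for this test, so there is no figure of that kind to reproduce.

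**Assumptions.** The before-after comparison is paired. In the ALT example, patients without injury change only by noise with mean 0 and SD 8 U/L. The rise of 400 U/L is illustrative. Neither figure comes from the protocol.

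**1. Smallest attainable signed-rank P.** The exact two-sided minimum is 2/2^n:
- n = 3: 2/8 = 0.25
- n = 4: 2/16 = 0.125
- n = 5: 2/32 = 0.0625
- n = 6: 2/64 = 0.031

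With 3 to 5 patients the signed-rank test therefore gives P > 0.05 whatever the data.

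**2. Paired-t power for a shift shared by all patients.** With a shift of d standard deviations of the change, power comes from the noncentral t with n − 1 degrees of freedom and noncentrality d√n.

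| n | d | d√n | critical t | power |
|---|---|---|---|---|
| 3 | 1 | 1.73 | 4.30 | 18% |
| 6 | 1 | 2.45 | 2.57 | 51% |
| 15 | 1 | 3.87 | 2.14 | 95% |
| 15 | 0.8 | 3.10 | 2.14 | 82% |
| 15 | 0.5 | 1.94 | 2.14 | 44% |

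A large common shift is usually found if all doses are pooled, and usually missed in a group of 3. Even pooled, a 0.5-SD shift gives P > 0.05 in 100 − 44 = 56% of trials.

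**3. Severe injury in a few of 15 patients.**
- *One patient, t test.* If one change is very large and the rest are negligible, t tends to 1. On 14 degrees of freedom P = 0.33, however large the rise.
- *Three patients at +400, t test.* Ignoring noise, the mean change is 3 × 400/15 = 80. The SD is √[(3 × 320² + 12 × 80²)/14] = √(384,000/14) = 165.6. Then t = 80/(165.6/√15) = 1.87, below the critical 2.14, and P = 0.08. Noise with SD 8 barely moves this, so about 100% of t tests give P > 0.05.
- *Three patients at +400, signed-rank test.* The three hold ranks 13, 14 and 15. At n = 15 the test rejects when the smaller rank sum is 25 or less (exact P = 0.048). The positive sum is at least 42, so the negative sum from the other 12 patients must be 25 or less. With pure noise that has probability 0.151, so P > 0.05 occurs in 0.849, about 85% (a 3,000-run simulation gave 84%).

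**4. A different noise model.** Simulating an ALT-like value with assumed log-scale SDs of 0.35 between and 0.2 within patients, and 5- to 20-fold rises, P > 0.05 occurred in 95–100% of trials with 1 of 15 injured, 91–100% with 2 and 82–100% with 3. With 8 or more of 15 injured it fell to 0–3%. The weakness concerns injury in a minority of patients.

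**5. What estimation would show instead.** With 0 events in n patients, the exact two-sided 95% upper limit is 1 − 0.025^(1/n): 71% at n = 3, 46% at n = 6, 22% at n = 15 and 19% at n = 18. The P value hides this uncertainty.

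**The case against.** The strongest reply is that the P > 0.05 clause does not stand alone. The sentence before it requires that organ function not be abnormal, and three patients with an ALT rise of 400 U/L would plainly breach that. The primary endpoint in section 3.2 is the incidence and severity of adverse events by CTCAE 5.0. Dose escalation rests on individual dose-limiting toxicities (section 5.1 and the DLT definition that follows it). Section 15.2, item 6, requires clinically significant laboratory changes to be recorded as adverse events and followed. This stands. A reader might infer that the product could be declared safe whatever happened to individual patients; the protocol does not support that.

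Two further limits also stand. It is tempting to say that a 3-patient group always passes, but that holds only for the signed-rank test. With all three patients at +400 and noise SD 8, the paired t is about 400/(8/√3) = 86.6, far above 4.30, and the test rejects. Nor does section 14.2 say that the test is run per dose. Read as pooled over about 15 patients, it has 95% power for a common 1-SD shift.

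These limits do not rescue the clause. The protocol ties the word safe directly to the non-significant result and does not make the individual-level conditions override it. If those conditions already decide the matter, the test adds only false reassurance; if they do not, the inference is invalid. Nor is this a detail left to the SAP, because the protocol itself fixes the rule.

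**Conclusion.** The concern holds for the P > 0.05 clause, not for the trial's safety assessment as a whole. The clause cannot support a conclusion of safety. Under a paired analysis the signed-rank version cannot signal harm in groups of 3 to 5, and the t version has 18% power at n = 3 and 51% at n = 6 for a 1-SD common shift. Pooled at n = 15, either version usually misses severe injury confined to one to three patients. A large shift shared by all patients would usually be found if doses are pooled.

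The minimum signed-rank P values depend only on n and pairing; the power figures also assume normally distributed changes. The injury percentages depend on the assumed noise and size of rise, although two different noise models give the same picture. The point should be fixed but is not critical, because the primary endpoint, the DLT rules and the escalation decisions do not depend on this test.

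**What to change.** Delete the sentence in section 14.2 that infers safety from P > 0.05. State that the safety conclusion rests on the individual-level adverse event, DLT and organ-function criteria already in the protocol. Report, by dose and overall:

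- baseline-to-worst CTCAE shifts for the liver and kidney values, from the chemistry already scheduled before enrolment and at W4, W8, W12 and W16;
- the number of patients with new grade 2 or higher, and new grade 3 or higher, liver and kidney abnormalities, with exact 95% confidence intervals;
- median changes with 95% confidence intervals, as description only;
- for the heart, the number of patients with new clinically significant ECG abnormalities, from the ECGs already scheduled before enrolment and at W16. The protocol names no numerical heart-function variable for the test.

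This needs no extra visit, sample or patient. The cost is a wording change, a few tables and a more modest safety claim, since even zero events among 15 patients leaves a true rate of up to 22% possible. Dropping the test also agrees better with the mainly descriptive analysis in section 5.23.
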